### Data collection

Primary data collection will occur on all patients who are transferred to a participating hospital following an OHCA. Trained in-hospital data collectors will complete chart abstraction of the variables related to post-arrest care for each of the hospitals. The data dictionary, containing all variables, definitions, and ranges specific to the study and abstraction instructions will be programmed into a touch icon that displays the information at the point of data entry for each variable to ensure standardization. Training prior to data collection will be completed through web-based seminars with ongoing training via email reminders and web conferences. A web-based data collection tool will be employed to facilitate data collection across the geographical regions.

The in-hospital data will also be linked to an existing local OHCA registry [21]. This registry currently captures complete pre-hospital data, including the Utstein variables for uniform reporting of adult and paediatric cardiac arrests [22]. This local data set includes patient demographics and survival status to hospital discharge on every OHCA brought to the 37 participating hospitals. A random sample of 10% of abstracted patient charts across all data guardians will be periodically re-abstracted by centralized research staff for quality assurance purposes. All data will be anonymized and handled according to national privacy legislation and its related regulations.

### Outcomes and analysis

The primary outcome will be the proportion of OHCA patients that achieve the target temperature within six hours of ED arrival. Secondary outcomes will include the following: proportion of eligible patients where cooling was initiated anywhere within the hospitals; proportion of eligible patients where cooling was initiated within six hours of ED arrival; proportion of eligible patients where cooling was initiated (ever) in the ED; survival to discharge; neurological outcomes at discharge (modified Rankin Score [23], Cerebral Performance Category Scale [24]); mean and median time to target temperature; mean and median temperature at six hours from first ED arrival; and mean and median (inter-quartile range) of duration of cooling.

We will also evaluate unintended consequences of our intervention; for example, proportion of ineligible patients cooled, and proportion of patients cooled with contraindications for cooling.

The primary analysis will be to compare hospitals receiving the active intervention to those receiving the passive intervention according to the stepped wedge schedule, and adjusting for clustering within hospitals and temporal trends. We will conduct sensitivity analyses where all the comparisons are of active hospitals versus passive hospitals versus retrospective hospitals (*i.e.*, before study implementation), and adjusting for clustering within hospitals and temporal trends. Other sensitivity analyses will compare hospitals receiving any knowledge translation intervention (*i.e.*, active and passive) versus hospitals without the intervention (*i.e.*, retrospective data collection prior to any knowledge translation intervention).

Additionally, all study outcomes and their relationship to factors that influence whether or not there is appropriate uptake of the study intervention to improve care of patients after OHCA will be evaluated. For example, we will examine the effects of organizational and system factors that might lead to an imbalance between wedges, or to differential rates of uptake of our intervention. These organizational and system factors could include (but are not limited to): academic versus community (affiliation with a university); urban versus rural (bed size); cardiac arrest volume high versus low; intensivist versus non-intensivist staffing; participation in the ICU Clinical Best Practices Demonstration Project [19]; capability to perform percutaneous coronary interventions within the hospital; method of cooling used by the hospital; and rate of withdrawal of life support within the hospital. For all primary and most secondary analyses, we will use generalized estimating equations (GEE) to adjust for the effects of clustering.

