### Sample size

During initial planning, there were insufficient data to perform a formal sample size calculation. Since the initial planning, we now have data from the one year retrospective collection from the participating hospitals that permit an approximation of study power. During recent years (2006 to 2008) the emergency medical services (EMS) in these regions transported approximately 1300 adults with OHCA to these destination hospitals. In 2008, 339 of these patients survived to be admitted to 30 of these hospitals, but only 10% were cooled to a body temperature less than 34 degrees Celsius within six hours of hospital arrival (intercluster correlation coefficient 0.09 estimated using variance components described by Hussey and Hughes [18]). The in-hospital mortality rate after successful resuscitation from OHCA is approximately 65% (range: 33% to 80% by institution). Assuming that a similar number of patients will be admitted to 37 hospitals in the network during two years of study, we anticipate that our study will have power (two-tailed Type I error probability 0.05) of at least 90% to detect an absolute increase of 1% or more in the proportion of patients that are successfully cooled to below 34°C within six hours of hospital arrival.

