### Study design

A stepped wedge cluster randomized trial design will be used to evaluate the impact of this intervention [18]. With this design, the intervention will be implemented sequentially to the participating hospitals over a number of equally spaced time periods. The order in which the participating hospitals receive the intervention (*i.e.*, enter the 'active' phase) will be determined at random and, by the end of the random allocation, all hospitals will have received the intervention. The study intervention is applied at the level of the hospitals (clusters), making it impossible to randomize individual clinicians using a traditional randomized controlled trial. We decided to use the stepped wedge design for randomizing these clusters because we anticipate that the study intervention will do more good than harm (making a parallel design cluster randomized trial, in which certain hospitals do not receive the intervention unethical). The stepped wedge design is also appealing because of the large scope and size of our study; for practical reasons, it would be difficult to deliver the intervention simultaneously to all hospitals. Finally, a stepped wedge design offers a number of opportunities for data analysis, particularly for modeling the effect of time on the effectiveness of an intervention [18]. The wedge randomization will be computer-generated by the statistician on the project (KT).

The unit of analysis in this study will be patients adjusted for clustering within individual hospitals. Hospitals participating in the SPARC Network will be randomized in groups of 6-8 and stratified according to ICU size (<10 beds versus ≥10 beds) and participation in another recent large-scale quality improvement project [19]. The phases of the trial and the stepped wedge design are depicted in Figure 2.

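### The stated primary GEE does not name the two stratification factors of the randomisation; adding both is nearly free and gains a little precision and protection against chance imbalance

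*Protocol article*

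**What the plan says.** In the protocol article, Study design randomises hospitals in groups, "stratified according to ICU size (<10 beds versus ≥10 beds) and participation in another recent large-scale quality improvement project". Outcomes and analysis defines the primary analysis as active against passive hospitals, "according to the stepped wedge schedule, and adjusting for clustering within hospitals and temporal trends", and repeats those two adjustments for the first sensitivity analysis. It later adds: "For all primary and most secondary analyses, we will use generalized estimating equations (GEE) to adjust for the effects of clustering".

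The same section plans a further evaluation: "we will examine the effects of organizational and system factors that might lead to an imbalance between wedges", or to differing uptake. Its open list of examples includes "participation in the ICU Clinical Best Practices Demonstration Project", which carries the same citation as the second stratifier. It also includes bed size, as a marker of urban versus rural. ICU size split at 10 beds is not on the list.

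Data collection links the in-hospital data to the local cardiac arrest registry: "This registry currently captures complete pre-hospital data, including the Utstein variables". That section also mentions demographics and survival to discharge. The article does not assign these variables to an adjusted comparison.

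**The concern.** When randomisation is stratified, the usual practice is to carry the stratifiers into the primary model, so that the analysis reflects the design. Here the adjustment set is written down and the stratifiers are not in it. A stepped wedge estimate uses contrasts between hospitals as well as within them. Stable differences between small and large ICUs, or between hospitals inside and outside the earlier project, can therefore add noise to it. How much depends on the weight the working correlation gives to between-hospital information.

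The article itself expects that hospital factors may be unbalanced between wedges, but deals with this beside the primary estimate, through an open-ended list. Naming the strata in the primary model settles in advance which hospital factors enter it. At stake is some efficiency and robustness, not the validity of the comparison.

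**Working it through.** **The plan's own figure.** The article gives no figure for the effect of the strata. Its only precision statement, in Sample size, is power of "at least 90% to detect an absolute increase of 1% or more in the proportion of patients that are successfully cooled", at "two-tailed Type I error probability 0.05". I could not reproduce it. With the standard errors (SE) below, power for 1 point is about 5%, for example Φ(1/3.28 − 1.96) = 4.9%. That is a separate matter, and adding the strata does not change it.

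**Inputs from the article.** 37 hospitals, four wedges, two years, 10% cooled at baseline, ICC 0.09, 339 patients admitted to 30 hospitals in 2008.

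**Assumptions.**
- Total N is 678 (2 × 339) or 836 (2 × 339 × 37/30).
- Five or six equal periods, since Figure 2 is not available.
- Wedges of 9/9/9/10, because four groups of 6 to 8 cannot hold 37 hospitals.
- Equal hospital sizes.
- The strata explain 0, 20% or 50% of the between-hospital variance. The article does not give this share.

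**Variance components.** Total variance 0.10 × 0.90 = 0.09. Between hospitals τ² = 0.09 × 0.09 = 0.0081. Within hospitals 0.0819, so a hospital-period mean has variance s = 0.0819/n with n = N/(37T). Adjustment for strata multiplies τ² by (1 − share) and leaves s unchanged.

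**Formulas.** Let U be the number of active hospital-periods, W the sum over periods of the squared number of active hospitals, V the sum over hospitals of the squared number of active periods, and I = 37.
- Exchangeable (Hussey-Hughes): Var = I·s(s + Tτ²) / [(IU − W)s + (U² + ITU − TW − IV)τ²].
- Independence weighting with the correct (sandwich) variance: Var = s/(U − W/I) + τ²(V − U²/I)/(U − W/I)².

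**Worked case, T = 5, N = 836.** U = 91, W = 2503, V = 271, s = 0.0819/4.519 = 0.01812.
- Exchangeable, share 0: 37 × 0.01812 × 0.05862 / (864 × 0.01812 + 2574 × 0.0081) = 0.03931/36.51 = 0.001077, so SE = 0.0328.
- Exchangeable, share 50% (τ² = 0.00405): 0.02573/26.08 = 0.000987, so SE = 0.0314.
- Independence, share 0: 0.01812/23.35 + 0.0081 × 47.19/545.3 = 0.001477, so SE = 0.0384.
- Independence, share 50%: 0.001127, so SE = 0.0336.

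**All cases** (SE in percentage points for shares 0 / 20% / 50%; reduction at 20% and 50%):

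| Periods, N | Exchangeable | Reduction | Independence | Reduction |
|---|---|---|---|---|
| 5, 678 | 3.60 / 3.55 / 3.44 | 1.4%, 4.3% | 4.07 / 3.90 / 3.62 | 4.3%, 11.2% |
| 5, 836 | 3.28 / 3.24 / 3.14 | 1.4%, 4.3% | 3.84 / 3.66 / 3.36 | 4.9%, 12.7% |
| 6, 678 | 3.83 / 3.79 / 3.70 | 1.1%, 3.4% | 4.30 / 4.13 / 3.87 | 3.9%, 10.0% |
| 6, 836 | 3.48 / 3.45 / 3.37 | 1.1%, 3.4% | 4.04 / 3.86 / 3.58 | 4.4%, 11.4% |

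In the worked case, power for a 10-point gain rises from Φ(0.10/0.0328 − 1.96) = 86.2% to Φ(0.10/0.0314 − 1.96) = 88.9% under exchangeable weighting with the strata explaining half.

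**Simulation.** Logistic GEE, exchangeable, stratified allocation, N = 836, 250 trials per scenario, all effects assumed (stratum log odds ratios 0.5 and 0.25, then 1.0 and 0.5; treatment 0.8). Without and with the strata, power was 77.6% and 78.4% (moderate strata), and 75.6% and 80.0% (strong). Null rejection was 6.8% and 7.6%, and 7.2% and 8.4%. Monte Carlo error is about 2.5 points for power and 1.6 for null rejection, so there is no clear change in either.

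The formulas do not know that allocation was stratified. Where stratification has already balanced the wedges, part of the gain has been secured by design, so the tabled reductions are best read as a ceiling.

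**The case against.** The strongest reply is that this is a condensed article. It names two adjustments and excludes no others, and a separate analysis plan may list the strata. That stands in part: a reader might infer that the model adjusts for nothing else, or that the strata are ignored, and the article says neither. The hospital-factor evaluation does cover project participation. What remains is that an adjustment set is stated for the primary analysis, the stratifiers are not in it, and the further evaluation is additional and omits ICU size as stratified.

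The second reply is that every hospital crosses from passive to active, so stable hospital characteristics largely cancel. Under exchangeable weighting this is nearly right, and the gain is small. Under independence weighting it is less so.

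Other stronger readings are also unsupported:
- That the omission biases the estimate or spoils the type I error. The simulation showed no clear effect on null rejection.
- That the strata were chosen because they predict uptake. Study design gives no reason for choosing them.
- That the 33% to 80% spread of hospital mortality in Sample size shows that patient covariates matter. It is an unadjusted spread between hospitals. If it came from about 339/30 = 11 patients per hospital (an assumption), the binomial SD at 65% would be √(0.65 × 0.35/11.3) = 14 points. The 47-point span is then about 3.3 SDs, which 30 hospitals could show by chance alone.

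Leaving patient covariates out is an efficiency and case-mix choice, not an error, and nothing in the article shows that they predict the process outcome.

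**Conclusion.** The point holds as a modest improvement to a stated analysis. The randomisation is stratified on two hospital factors, and the stated primary GEE names neither. This forgoes an SE reduction of about 1% to 4% (exchangeable) or 4% to 13% (independence), together with some insurance against chance imbalance between wedges. The ranges rest on the strata explaining 20% to 50% of the between-hospital variance, on a complete four-wedge layout with five or six periods, and on 678 to 836 patients. None of these is fixed by the article as shown. If a separate analysis plan already includes both factors in the primary model, the point is closed.

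**What to change.** Add one sentence to Outcomes and analysis: the primary GEE includes ICU size (<10 versus ≥10 beds) and participation in the earlier quality improvement project as fixed covariates, beside the period terms. If they are left out on purpose, say why. The cost is two degrees of freedom among 37 hospitals, and the data are already held because they were needed for the randomisation.

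As a lesser point, for survival and neurological outcome, prespecify a short list of variables fixed before hospital arrival, drawn from the registry demographics and Utstein variables. Report the estimate without patient covariates alongside. The small downside is that a logistic model then gives a conditional rather than a marginal odds ratio, so the report should say which is which and the plan should say how missing covariate values are handled.

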## Methods/design

### The setting

The hospitals in this project include the 33 southern Ontario hospitals already participating in the University of Toronto regional coordinating centre site of the Resuscitation Outcomes Consortium (ROC), as well as 4 community hospitals from the regions of York and Simcoe. ROC is an international research collaborative studying interventions that may improve survival from OHCA [16,17]. Because the EDs of these hospitals are already engaged in out-of-hospital resuscitation research, participation in the Strategies for Post-Arrest Care (SPARC) Network is a natural extension of this research to include in-hospital care and ICUs. These 37 hospitals provide care to a population of 8.8 million people who live within eight regions of the Province of Ontario, and have hospital bed capacities ranging from 19 to >600 and ICU bed capacities ranging from 4 to 42. This sample also includes all of the adult teaching hospitals affiliated with McMaster University and the University of Toronto.

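### If the GEE analysis is run in its ordinary uncorrected form, 37 hospitals and few events give a type I error of about 8% for the primary outcome instead of the planned 5%

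*Protocol article*

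**What the plan says.** The Protocol article, under Outcomes and analysis, compares active with passive hospitals along the stepped wedge schedule, adjusting for clustering and temporal trends. For the primary and most secondary analyses it says "we will use generalized estimating equations (GEE) to adjust for the effects of clustering". Nothing is said about the variance estimator, working correlation, reference distribution or a small-sample correction.

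The Sample size section gives the error level as a "two-tailed Type I error probability 0.05". It also supplies the figures that determine how well GEE will behave: "In 2008, 339 of these patients survived to be admitted to 30 of these hospitals", of whom "only 10% were cooled to a body temperature less than 34 degrees Celsius within six hours of hospital arrival", with an "intercluster correlation coefficient 0.09 estimated using variance components described by Hussey and Hughes". The trial has 37 hospitals in four wedges. On their size, The setting gives only "hospital bed capacities ranging from 19 to >600 and ICU bed capacities ranging from 4 to 42".

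**The concern.** The robust (sandwich) variance in GEE is justified as the number of clusters grows. With few clusters it tends to be too small, because the residuals it uses have already been pulled towards zero by fitting the model. Comparing the resulting statistic with a normal distribution then ignores the uncertainty in the variance itself. Both errors make rejection too easy.

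Here the effective sample is 37 hospitals. Exposure varies only by hospital and period, period effects must be estimated as well, and the outcome is uncommon. If the ordinary form is used, a null intervention would be declared effective or harmful more often than the 5% the plan sets, and the confidence interval for the primary effect would be too narrow.

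**Working it through.** **The plan's own figure.** The 5% is a chosen level, so there is nothing to reproduce. The check is whether the named method delivers it. (The power claim beside it, "at least 90% to detect an absolute increase of 1% or more in the proportion of patients", does not reproduce from the stated inputs. That is a separate matter and nothing here depends on it.)

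**Inputs from the article.** 37 hospitals, four wedges, two years, 10% baseline, ICC 0.09, and 339 patients a year in 30 hospitals.

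- Patients, lower figure: 2 × 339 = 678, or 678 / 37 = 18.3 per hospital.
- Patients, scaled to 37 hospitals: 2 × 339 × 37 / 30 = 836, or 836 / 37 = 22.6 per hospital.
- Expected events under no effect: 0.10 × 678 = 68 to 0.10 × 836 = 84.

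**Assumed.** Wedges of 9/9/9/10; six periods (five and eight also tried); coefficient of variation (CV) of hospital volume 0.6 (0 and 0.9 also tried).

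**Model.** Under no effect, logit(p_i) = −2.56 + b_i with b_i normal, SD 0.99, calibrated to a 10% rate and ICC 0.09. Each simulated trial was analysed by logistic GEE with period terms and exposure. The uncorrected variance is B⁻¹ (Σ D_i′V_i⁻¹ r_i r_i′ V_i⁻¹ D_i) B⁻¹, with B = Σ D_i′V_i⁻¹D_i. Mancl-DeRouen replaces r_i by (I − H_i)⁻¹ r_i, where H_i is the hospital's leverage matrix. The t reference has K − p degrees of freedom (hospitals minus regression coefficients): 37 − 7 = 30 in the base case. The code agreed with a standard GEE package to four decimals on eight trials.

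**Results.** 5,000 trials per scenario, Monte Carlo SE about 0.4 points:

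| Scenario | Uncorrected, normal | Mancl-DeRouen, t |
|---|---|---|
| Base: 836 patients, CV 0.6, exchangeable | 8.3% | 5.1% |
| Equal hospital sizes | 8.3% | 5.4% |
| CV 0.9 | 8.6% | 4.9% |
| 678 patients | 7.8% | 4.9% |
| 678 patients, CV 0.9 | 9.5% | 5.7% |
| Independence working correlation | 9.1% | 5.2% |
| Independence, CV 0.9 | 9.9% | 5.3% |
| Five periods | 8.4% | 5.0% |
| Eight periods | 7.9% | 4.7% |
| Linear time | 8.3% | 5.9% |
| Passive-only control periods | 7.6% | 4.0% |
| ICC 0.02 | 7.5% | 4.7% |
| 20% rate | 6.9% | 4.1% |
| 1,300 patients | 6.9% | 4.3% |

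Over all 18 scenarios the uncorrected test ran from 6.9% to 9.9%, and Mancl-DeRouen with t from 3.8% to 5.9%. The 3.8% comes from a sparse scenario (678 patients, CV 0.9, independence, passive-only controls) in which 640 of 5,000 fits failed, so it is the least reliable entry.

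Neither half of the correction is enough alone. In the base case the uncorrected variance with t gives 7.1%, and Mancl-DeRouen with a normal reference gives 6.1%. Kauermann-Carroll with t gives 6.2%.

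**Standard errors.** In 600 further base-case trials the mean uncorrected SE was 0.384 against an empirical SD of 0.416: 0.384 / 0.416 = 0.923, about 8% too small. The mean Mancl-DeRouen SE was 0.416. As a cross-check, 2 × [1 − Φ(1.96 × 0.923)] = 2 × [1 − Φ(1.809)] = 7.0%. The understated SE thus accounts for most of the excess, and the rest is consistent with the SE varying from trial to trial.

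**Further simulations.** One with beta-binomial hospital effects and five periods (2,400 null trials) gave 7.8% uncorrected and 4.6% with Mancl-DeRouen and t on 35 degrees of freedom. Another 2,400 null trials gave 7.8% and 5.0%, and 7.2% uncorrected with equal hospital sizes.

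**The case against.** The strongest objection is that the article never says the uncorrected form will be used. GEE with a Mancl-DeRouen variance and a t reference is still GEE and fits the sentence as written. A variance option is the kind of detail an article leaves to the full protocol or analysis plan, neither of which is shown. This stands as a limit: a reader might infer that the trial's actual type I error is 8%, and the documents do not support that. What remains is that GEE is named without qualification for a 5% test, and its ordinary form missed that level in every scenario tried.

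A reader might also blame the unequal sizes of the hospitals. The documents do not support this either. Bed ranges are not arrest volumes, no patient numbers per hospital are given, and equal sizes gave the same 8.3%. Strong inequality adds something (9.5% against 7.8% with 678 patients) but is not the main driver.

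A third inference would be that every interval in the trial is too narrow. Only one binary outcome near 10% was simulated. Survival, with in-hospital mortality of about 65%, and the time and temperature outcomes were not.

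Finally, parts of the design are assumed. Figure 2 is not available, and the article's four wedges drawn in groups of six to eight would hold 4 × 6 = 24 to 4 × 8 = 32 hospitals rather than 37. The 10% is a 2008 rate, and passive hospitals, which receive a visit and a protocol copy, may do better. At 20% the excess shrinks to 6.9% but does not vanish.

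**Conclusion.** The point holds conditionally. If the GEE analysis of the primary outcome uses the uncorrected sandwich variance and a normal reference, its type I error is about 8% (roughly 7% to 10% over the assumed scenarios) instead of 5%, with standard errors about 8% too small. The cause is mainly the limited number of hospitals and the sparse events.

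This rests on the article's 10% rate, ICC of 0.09 and 37 hospitals, on 678 to 836 patients, and on the assumed wedge sizes and periods. Applying the eligibility criteria could take the analysed number below 678, which was not simulated. The excess is moderate, about three extra false positives per 100 null trials. It deserves a correction before analysis but does not undermine the design.

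**What to change.** State, or confirm if the full plan already does so, that the GEE analysis of the primary outcome uses a small-sample bias-corrected sandwich variance such as Mancl-DeRouen, with a t reference based on the number of hospitals. Fix the degrees of freedom in advance. Hospitals minus the number of regression coefficients held close to 5% across the scenarios above, and hospitals minus 2 (35) gave 4.6% and 5.0% in the further simulations. Apply the same option to the other GEE analyses for consistency.

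The change is one sentence and one software setting; design and data collection are untouched. The price is a wider interval. In the base case the factor is 0.416 / 0.384 = 1.083 from the variance and 2.042 / 1.960 = 1.042 from t on 30 degrees of freedom, so 1.083 × 1.042 = 1.13, or about 13% wider. Some apparent power is lost accordingly, which is the cost of holding the stated error level.
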